Both cohorts will collect 3 months of retrospective baseline data collection before beginning the study. During the first six months of the intervention, the practice groups randomized to Cohort 1 will begin working on improving HTN practices within their clinic via a QIC, while the other cohort will act as a control (usual care) with data collection (**Specific Aim 1**). Cohort 1 will attend an initial 1-day interactive video webinar learning session where they will learn QI methodology, enhance and practice QI skills, identify local 30-60 day aims to improve local HTN practices and increase their understanding of pediatric HTN. They will also begin tracking data on a HTN registry and learn how to ensure accurate BP measurement is completed in their clinic. They will participate in QI coaching, monthly video conferences, and monthly mini-root cause analyses (Mini-RCA) (see below). Cohort

2 will submit control data and not receive centralized data feedback. They will also begin tracking data on a HTN registry and learn how to ensure accurate BP measurement is completed in their clinic.

During the second 6 months, Cohort 1 will integrate their HTN subspecialist into the QIC and focus on issues at the boundary of PCP and subspecialty care (e.g. pre-referral work-up, communication across providers, and time for next available appointment). Cohort 2 will begin improving HTN practices within their clinics via a separate but comparable PCP-only QIC, (**Specific Aim 2**). In the third 6 months, Cohort 1 will continue QIC components and implement a hub and spoke model, where the PCP diagnoses and provides definitive management for pediatric HTN with subspecialist support and Cohort 2 will engage their HTN specialist (**Specific Aim 3**). In the final six months, Cohort 1 will sustain their changes, illustrating the durability of these system changes even after QIC completion. Cohort 2 will continue their QIC with the hub and spoke model.

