#### 4. Pediatric HTN Outcome Measures:

The research team has developed clearly defined primary and secondary outcome measures for pediatric HTN diagnosis and management errors, and has experience using evidence-based tools for their improvement. All outcome measures are described in Table 2. **Error! Reference source not found.** These measures will be compared between usual care, QIC without subspecialist involvement, QIC with subspecialist involvement, and hub and spoke QIC. The primary outcome is pediatric HTN or EBP diagnosis and management errors, defined as the number of patients with an elevated systolic or diastolic BP for age, sex and height (defined as  $\geq 90^{\text{th}}$  percentile for age, sex and height or  $>120/80$ , whichever is lower, in  $\geq 3$  year old patients) who did not have all correct diagnostic

and management decisions completed per 100 patients with an elevated BP measured across all 3 intervention conditions versus usual care (control) condition. Each practice site will identify the first 10 patients seen in their site monthly with an elevated BP and then evaluate those patients following the elevated BP to confirm correct HTN and EBP diagnosis and management steps. During the baseline period, this number will be 17 patients per month for 3 months, in order to provide an adequate baseline sample for practices to begin changing their practice. For example, if a patient already had one elevated BP reading in the Stage 1 HTN range and then presented for care, the practice site would record if they 1) received a repeat BP measurement in 1-2 weeks, 2) four extremity BP measurements and 3) a scheduled appointment for a repeat BP measurement in 3 months, etc... Similarly, if a patient already had 3 BPs in the Stage 1 HTN range and then presented to the practice site, this measure would track whether they received 1) all appropriate laboratory testing, 2) a subspecialist referral, and if diagnosed with HTN, 3) management with a recommended antihypertensive medication. In this way practice sites will be able to feasibly collect data, receive real-time and actionable data feedback, and work to reduce harmful errors. We acknowledge that HTN error measurement in the control period may introduce an intervention effect, but we have no reason to believe this effect will be different between the intervention and control practices.

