As Secondary Outcome Measures, we will also track each of these markers of correct care individually and the time to completion from initial elevated BP measurement to each marker. This allows us to investigate how the different QIC conditions affect the proportion of patients who receive guideline recommended care, which diagnostic and management steps are correctly implemented, and the time it takes for patients to receive this care. We can then test error rate and time to care improvement between usual care, the QIC without subspecialist involvement, the QIC with subspecialist involvement, and the hub and spoke model QIC.

In order to confirm appropriate screening, practices will perform anonymous self-audits on the 5 most important aspects of BP measurement (a. choosing children to screen as per 2017 guideline recommendations; b. positioning and calming a child for BP measurement; c. choosing an appropriately sized BP cuff; d. inflating the cuff to the appropriate pressure, and e. documenting percentiles and interpreting when the BP is elevated based on cumbersome age, sex and height tables) during the first 6 months of the project: either the initial local QIC without subspecialist involvement or during the baseline collection period for the control group. This anonymous self-audit will occur weekly for each person who shares primary responsibility for measuring pediatric blood pressures at triage. These data will be submitted anonymously into REDCap.

Finally, as noted above, we will compare time to 3rd next available appointment for pediatric patients to subspecialist clinics in order to assess the effects of pediatric primary care providers referring and managing different types of patients with hypertension.

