| Primary Outcome Measure    | Number of patients without all correct diagnostic and management decisions (Figure 4) per 100 patients with measured elevated BP                                                                                                                                                                                                                                                                                                                                                                                                                                                                                                                                                                                                                                                                                                                                                                                                                         |
|----------------------------|----------------------------------------------------------------------------------------------------------------------------------------------------------------------------------------------------------------------------------------------------------------------------------------------------------------------------------------------------------------------------------------------------------------------------------------------------------------------------------------------------------------------------------------------------------------------------------------------------------------------------------------------------------------------------------------------------------------------------------------------------------------------------------------------------------------------------------------------------------------------------------------------------------------------------------------------------------|

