| Secondary Outcome Measures | 
 
1. Number of patients without correct diagnostic and management decisions at specified points per 100 patients with measured elevated BP 
 
a. Re-measuring BP twice in clinic via auscultation
 
b. Weight and nutrition counseling
 
c. Repeat BP measurement visits appropriately timed
 
d. Initial laboratory workup
 
e. Subspecialist referral
 
f. Definitive medication management initiation
 
 
 
2. Mean time from first elevated BP to specific points in diagnostic and management process (see #1 above)
 
3. Number of BPs measured correctly with appropriately screened patient, patient position, cuff size, inflation, BP percentiles correctly documented and interpreted per 100 observations conducted
 
4. Time to 3rd next available subspecialist appointment
 
 |

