### **Important Definitions:**

- **Manual Blood Pressure:** auscultatory measurements taken with a stethoscope.
- **Years:** As it refers to age, round to nearest half year (i.e., patient that is 4 years, 3 months old would be charted as 4.5 years old; patient that is 9 years, 2 months old would be charted as 9 years old).
- **How many elevated BPs did the patient have at unique visits?:** In last 24 months, how many visits (healthcare maintenance or non-acute) did the patient have elevated BPs? A unique visit occurs on separate days. e.g. If patient had an elevated BP on Monday 12 months prior and came back on Tuesday 12 months prior and also had an elevated BP and neither visit include a normal BP at THAT visit, this patient would have 2 prior unique visits with an elevated BP. “This visit” would be the patient’s “Third Elevated BP.”
- **BP in Elevated Blood Pressure Range:**  $\geq 90^{\text{th}}$  to  $< 95^{\text{th}}$  Percentiles or 120/ $< 80$  to 129/ $< 80$
- **BP in Stage I Hypertension Range:**  $\geq 95^{\text{th}}$  to  $< 95^{\text{th}} + 12\text{mm}$  or 130/80 to 139/89
- **BP in Stage II Hypertension Range:**  $\geq 95^{\text{th}} + 12\text{mm}$  to  $< 95^{\text{th}} + 30\text{mm}$  or  $\geq 140/90$  to  $< 180/120$
- **BP warranting immediate referral:**  $\geq 95^{\text{th}} + 30\text{ mmHg}$  or  $\geq 180/120$  or patient with symptoms
- **Subspecialist:** Nephrologist or Cardiologist.
- “No” means the same as “Not Documented”
- **Was a referral request to a subspecialist made?:** did the PCP or other office staff tell the patient or write a specific note for the patient suggesting they need to go see a subspecialist provider?
- **Date the referral request to a subspecialist was made:** The date the provider or other person told/wrote that the patient should go to the subspecialist is the “date” the referral was made. This is not the appointment date that the patient may have received. This is not the date the patient actually went to the subspecialist.

- **Date of first specialist visit completed:** date patient saw a subspecialist for the first time. NOTE: Only applies to completed visits; scheduled visits which result in a no-show do not count.
- **Weight counseling:** discussion of the need to lose weight
- **Nutrition counseling:** discussion of healthy foods and/or need to eat less salt
- **Lifestyle modifications:** move more, less screen time, etc.

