5. Did provider document that the following were discussed with patient and/or family:

5a. Weight counseling ☐ Yes ☐ No ☐ N/A patient has normal BMI

5b. Nutrition counseling ☐ Yes ☐ No

5c. Lifestyle modifications ☐ Yes ☐ No

6. Did the patient have BP in Stage II Hypertension range ( $\geq$ 95th+12mm to <95th+30mm; or  $\geq$ 140/90 to <180/120)?

☐ Yes [Go to 6a] ☐ No [Go to 7]

6a. If patient had BP in Stage II Hypertension range ( $\geq$ 95th+12mm or  $\geq$ 140/90) were both upper extremities and 1 lower extremity blood pressure taken and documented?

☐ Yes [Go to 6b] ☐ No [Go to 7]

6b. If yes, were they normal? ☐ Yes [Go to 7] ☐ No [Go to 6c]

6c. If abnormal, was a referral request to a subspecialist made? ☐ Yes [Go to 6d] ☐ No [Go to 7]

\*Did someone in the clinic tell the patient/family they needed to see a subspecialist and complete referral paperwork?

6d. If a subspecialist referral was made, which specialist? (Check all that apply):

☐ Nephrologist ☐ Cardiologist ☐ Other: \_\_\_\_\_

6e. ☐ N/A: Patient never attended subspecialist visit [Go to 7]

[IF N/A NOT CHECKED] Date first subspecialist visit completed (MM/DD/YYYY): \_\_/\_\_/\_\_\_\_ [THESE DATA ARE ENTERED INTO REDCAP BUT NOT GIVEN TO RESEARCH TEAM]

\*Not date referral request made, but date patient actually saw subspecialist

6f. Date information on the patient was received from subspecialist back to the pediatrician:

(MM/DD/YYYY): \_\_/\_\_/\_\_\_\_ [THESE DATA ARE ENTERED INTO REDCAP BUT NOT GIVEN TO RESEARCH TEAM]

\*If same electronic health record, enter date note was signed by the subspecialist

7. Was a follow-up appointment recommended or made for the patient with the primary care practice?

☐ Yes [Go to 7a] ☐ No [Go to Section D]

7a. If yes, what date was the follow-up appointment scheduled for? (MM/DD/YYYY): \_\_/\_\_/\_\_\_\_ [THESE DATA ARE ENTERED INTO REDCAP BUT NOT GIVEN TO RESEARCH TEAM]

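### Uncharted counselling is scored as not done and feedback differs by condition, so part of the usual-care versus QIC difference could be charting

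*Protocol*

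**What the plan says.** **Scoring.** The Appendix (Important Definitions) states "No” means the same as “Not Documented". In the chart review tool, item 5 of sections C, D and E asks "Did provider document that the following were discussed with patient and/or family", followed by weight counselling (5a), nutrition counselling (5b) and lifestyle modification (5c).

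**Outcome.** Table 2 defines the primary outcome as "Number of patients without all correct diagnostic and management decisions (Figure 4) per 100 patients with measured elevated BP". "Weight and nutrition counseling" is item 1b of the secondary outcomes, and section 4 introduces those with "we will also track each of these markers of correct care individually".

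**Feedback.** Section 3 says that Cohort 2, in its usual-care phase, "will submit control data and not receive centralized data feedback". Table 1 and the Data and Safety Monitoring Plan give intervention practices monthly reports with benchmarking. Table 1 also gives them a monthly mini-root cause analysis of one error.

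**Measurement effect.** Section 4 concedes that measuring errors in the control period may itself act as an intervention, but adds that "we have no reason to believe this effect will be different between the intervention and control practices".

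**The concern.** Item 5 measures charting. No other field on the form can show that counselling took place. In an all-or-nothing outcome, one unwritten item can turn a chart that is otherwise fully correct into an error.

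Feedback scored from the chart rewards writing things down as well as doing them, and it reaches only practices in a QIC. If charting improves faster there than under usual care, the recorded error rate falls with no change in care. The model in section 6.1 cannot separate the two, because documentation-only items sit in the same binary outcome as steps that leave a system record.

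The planned checks do not help. Searching the whole record and having site leads re-review charts can find only what was written, and the data are unblinded and abstracted by the practices. Section 6.4 lists variable data collection methods as a limitation, but not charting that responds to feedback.

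The contrast at stake is usual care against the first QIC (Aim 1), in the first six intervention months. Section 3 says the data from November 2018 to March 2020 will be analysed and published.

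**Working it through.** **1. The plan's own yardstick.** Section 6.3 claims more than 80% power for a fall of 3 percentage points per dose step. An approximate check used a linear dose with generalised least squares variance, 60 sites in 7 groups, 24 months, 10 charts per site-month, error rate 0.73, ICC 0.5 and uniform ±15% variation (variance 0.15²/3 = 0.0075 per level). The sustain phase was taken as dose 3, which is an assumption. Power = Φ(0.03/SE − 1.96).
- No month effect shared across sites: SE about 0.009, power 0.90 to 0.92.
- A month effect shared by all sites: SE 0.0182, power 0.38.

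The protocol does not say which was simulated, so the 3-point figure is neither confirmed nor rejected. It serves below only as the plan's stated benchmark.

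**2. Effect of charting with care unchanged.** Let T be the true all-correct proportion, and d the probability that counselling is charted when all care was truly correct (d0 under usual care, d1 under the QIC). Charting of the other steps is held fixed. Recorded all-correct under usual care is 1 − 0.73 = 0.27 = T × d0, so T = 0.27/d0. Under the QIC it is 0.27 × d1/d0. The spurious fall in error is 27 × (d1/d0 − 1) points.

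The documents give no value for d, so these are assumed ranges:

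| d0 | d1 | Recorded error under QIC | Spurious fall | Implied T |
|---|---|---|---|---|
| 0.9 | 1.0 | 70.0% | 3.0 points | 30.0% |
| 0.8 | 0.9 | 69.6% | 3.4 points | 33.8% |
| 0.7 | 0.9 | 65.3% | 7.7 points | 38.6% |
| 0.6 | 0.9 | 59.5% | 13.5 points | 45.0% |

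**3. Rise needed to reach the protocol's figures.**
- 3 points: (27 + 3)/27 = 1.11, a relative rise of about 11%.
- 9 points (usual care to hub and spoke in section 6.3): 36/27 = 1.33.
- Hypothesis 1, a 50% reduction from 73% to 36.5%: (27 + 36.5)/27 = 2.35. Since d1 cannot exceed 1, d0 could be at most 1/2.35, about 0.43.

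**4. The same thing as a ceiling.** If a share f of the recorded errors are errors only because counselling was uncharted, charting alone can lower the rate by at most 73 × f points: 3.65 points at f = 5% and 7.3 points at f = 10%.

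**The case against.** Several points on the other side stand.

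- **Control sites also see the chart.** A reader might infer that documentation can improve in one arm only. The protocol does not support that. Both cohorts abstract 10 charts per site per month with the same tool, keep a registry and are taught accurate BP measurement, so some gain is likely under usual care. The claim is only that the gain may be larger under the QIC.
- **The feedback is on performance.** The protocol describes data feedback, not documentation feedback. It bears on charting because performance is scored from the chart.
- **Section 4 is not contradicted.** A reader might take the equal-effect sentence as refuted by the feedback difference. The sentence concerns the effect of measuring, which both arms do, and feedback is a component of the intervention. The difference weakens the reassurance but does not make the sentence false.
- **Counselling is reported separately.** Table 2 sets out items 1a to 1f as secondary outcomes, so a gain confined to counselling would be visible. Those results do not, however, give the composite without counselling.
- **Membership of the composite is inferred.** The figure that defines all correct decisions is not shown, and the worked examples in section 4 do not mention counselling. Its inclusion rests on Table 2 and the sentence introducing the secondary outcomes.
- **Other steps rest on charting too.** A referral request is defined by what staff told the patient or wrote, and follow-up counts if recommended or made. Dropping counselling alone would leave part of the problem in place.

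**Conclusion.** The point holds as a limited one. Part of the usual-care versus QIC risk difference could be charting, and the protocol plans nothing that would show how much. Under assumed charting rates the artefact is 3.0 to 13.5 points in the scenarios above; a relative rise of about 11% is enough to match the stated detectable step.

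This rests on counselling being part of the composite, on charting improving more under feedback than without it, and on charting rates that the documents do not give.

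A reader might go further and infer that the whole hypothesised effect could be an artefact. That is unlikely: it would need usual-care charting of about 43% or less among patients whose care was truly all correct, rising to nearly complete. Nor does the concern apply equally to Aims 2 and 3, because all three QIC conditions receive feedback.

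**What to change.** **Section 6.1.** Add a sensitivity analysis with the same model, using an error proportion scored without items 5a to 5c and limited to steps with a system-generated trace: resulted laboratory and imaging dates, completed subspecialist visit dates, medication order dates and scheduled appointment dates. Leave out referral requests and follow-up that was only recommended, since these rest on what was told or written. Report it beside the unchanged primary outcome and read it together with the item-level secondary outcomes. Set no fixed agreement rule: counselling is genuine care that a QIC may improve, so the two risk differences can legitimately differ.

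**Section 4.** Keep the equal-effect sentence but qualify it, stating that feedback differs by condition and may change documentation differently.

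**Cost.** One extra model on fields already collected, and one edited sentence. The restricted version omits real care and has a different base rate. For charts that end at the first elevated reading it rests mainly on the scheduled appointment date. It therefore accompanies the primary outcome and does not replace it.

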## BP-CATCH CHART REVIEW TOOL

v. 3 11/28/18

Patient Information: **FOR CLINIC USE ONLY; NOT ENTERED INTO REDCap**

1. Patient Last Name: \_\_\_\_\_  
2. Patient First Name: \_\_\_\_\_  
3. MRN: \_\_\_\_\_  
4. Date of Birth (MM/DD/YYYY): \_\_/\_\_/\_\_\_\_  
5. Patient's chart FIRST reviewed on (MM/DD/YYYY): \_\_/\_\_/\_\_\_\_  
6. REDCap Record ID: \_\_\_\_\_

**EXCLUDE Patients:** not at healthcare maintenance visits or non-acute care visits, prior hypertension/elevated BP diagnosis, prior diagnosis of congenital heart disease, Chronic Kidney Disease, urologic disease, or organ transplant, BP ≥ 95th percentile + 30mm or >180/120 or symptomatic patient, previously included in BP-CATCH data entry

**A. Patient Demographic Information**

1. Patient age (in years) at **this visit**: \_\_\_\_\_ years (round to nearest 0.5 year)  
2. Patient's Race: ☐ White ☐ Black ☐ Asian ☐ Native American/Alaskan Native ☐ Multiple Races ☐ Unknown  
3. Patient's Ethnicity: ☐ Not Hispanic ☐ Hispanic ☐ Unknown  
4. Patient's Insurance Status: ☐ Private ☐ Public ☐ Uninsured/Self Pay ☐ Unknown  
5. Patient's Sex: ☐ Male ☐ Female

**B. How Many Elevated BPs at Unique Visits in the Last 24 Months?**

1. In the last 24 months, at healthcare maintenance and/or non-acute care visits, how many elevated BPs did the patient have at unique visits? Please count total number of unique visits with abnormal BPs and no normal BPs at those visits in the last 24 months at a healthcare maintenance or non-acute care visits and check appropriate box

**Note:** A patient may also have one or more normal BPs at separate unique visits in the last 24 months at healthcare maintenance or non-acute care visits and be included.

- ☐ This visit is their **First elevated BP** [Go to Section C]  
☐ This visit is their **Second elevated BP** [Go to Section D]  
☐ This visit is their **Third elevated BP** [Go to Section E]  
☐ This visit is their **Fourth or more elevated BPs** [Go to Section E]  
☐ This visit is their first visit to this clinic or in our EHR. Therefore, this visit is their **First elevated BP** [Go to Section C]

